## Abstract

**Introduction:**

Histological diagnosis of malignant mesothelioma requires an invasive procedure such as CT-guided needle biopsy, thoracoscopy, video-assisted thorascopic surgery (VATs) or thoracotomy. These invasive procedures encourage tumour cell seeding at the intervention site and patients can develop tumour nodules within the chest wall. In an effort to prevent nodules developing, it has been widespread practice across Europe to irradiate intervention sites postprocedure—a practice known as prophylactic irradiation of tracts (PIT). To date there has not been a suitably powered randomised trial to determine whether PIT is effective at reducing the risk of chest wall nodule development.

**Methods and analysis:**

In this multicentre phase III randomised controlled superiority trial, 374 patients who can receive radiotherapy within 42 days of a chest wall intervention will be randomised to receive PIT or no PIT. Patients will be randomised on a 1:1 basis. Radiotherapy in the PIT arm will be 21 Gy in three fractions. Subsequent chemotherapy is given at the clinicians’ discretion. A reduction in the incidence of chest wall nodules from 15% to 5% in favour of radiotherapy 6 months after randomisation would be clinically significant. All patients will be followed up for up to 2 years with monthly telephone contact and at least four outpatient visits in the first year.

**Ethics and dissemination:**

PIT was approved by NRES Committee North West—Greater Manchester West (REC reference 12/NW/0249) and recruitment is currently on-going, the last patient is expected to be randomised by the end of 2015. The analysis of the primary end point, incidence of chest wall nodules 6 months after randomisation, is expected to be published in 2016 in a peer reviewed journal and results will also be presented at scientific meetings and summary results published online. A follow-up analysis is expected to be published in 2018.

**Trial registration number:**

ISRCTN04240319; NCT01604005; Pre-results.

Strengths and limitations of this studyLargest, adequately powered randomised controlled study of prophylactic radiotherapy in this population.Radiotherapy fields reflect current practice for thoracoscopy and drain insertion.Monthly telephone follow-up to supplement out-patient follow-up clinical significance of chest wall metastases measured with visual analogue scale pain score.Will not determine role of prophylactic radiotherapy at the site of an indwelling pleural catheter.

## Introduction

Malignant pleural mesothelioma (MPM) is almost exclusively linked to asbestos exposure with a latency period that is usually more than 30 years and prognosis is poor.^1–4^ The median survival in the UK is 8.8 months and the 1-year survival 38.5%.^5^

Diagnosis of mesothelioma is usually made by pleural biopsy either via CT-guided needle biopsy, thoracoscopy, video-assisted thoracic surgery (VATs) or thoracotomy. Patients often have associated pleural effusions and require chest drains to relieve symptoms such as chest pain and difficulty breathing. These invasive procedures encourage tumour cell seeding at the site of the intervention, which can result in formation of a subcutaneous tumour. The rate of chest wall metastases ranges from 2% to 50%, and depends on the procedure performed.^4^
^6–14^

In an effort to minimise tumour seeding and prevent nodule development, it has been widespread practice for more than 20 years in the UK to irradiate intervention sites postprocedure—a practice known as prophylactic irradiation of tracts (PIT).

Only three randomised controlled trials, the largest with 61 patients, have assessed the role of PIT with conflicting results reported.^14–19^ One study reported a statistically significant reduction in the frequency of malignant seeding of tracts in the PIT arm compared to the control arm^14^; the other two studies did not.^15^
^16^ Systematic reviews of the literature have concluded that the randomised trials conducted to date were considered the best available evidence for PIT, but that there was insufficient evidence to definitively recommend PIT.^17–20^ Inconsistencies are also evident in current national recommendations on the use of PIT. The British Thoracic Society^21^ recommends the use of PIT to prevent chest wall nodule formation following an interventional procedure. In contrast, the Cancer Care Ontario Programme^22^ stated that a recommendation for PIT in MPM could not be made due to inconsistent evidence, reflecting a lack of high-quality data. Similarly, in 2010 the European Respiratory Society stated “The value of prophylactic radiotherapy is questionable”^23^ and the European Society of Medical Oncology (ESMO) clinical recommendations for diagnosis, treatment and follow-up of MPM state that “it remains impossible to draw definitive conclusions regarding its efficacy”.^24^

Currently in the UK the routine use of PIT in patients with MPM depends on locality. A 2008 UK survey showed that 75% of radiotherapy centres are routinely using PIT.^17^ In addition, the small number of patients recruited to each arm, the high death rates, and overestimation of the rate of chest wall metastasis in the control arms, question whether the three previous randomised controlled trials were adequately powered. Furthermore, recent evidence shows that portal tracts are not always perpendicular to the skin^25^ and thus the small radiation fields centred on the chest wall scar employed by the previous negative studies may have been suboptimal.

There is now strong evidence to support the role of palliative chemotherapy in patients with MPM^26^ which is approved in the UK by the National Institute of Clinical Excellence (NICE).^27^ Importantly, the previous studies were conducted before palliative chemotherapy was widely used in MPM. Therefore, the role of PIT in the era of effective palliative chemotherapy remains undefined. In addition, no previous studies have used validated pain scoring tools to assess pain from tract metastases.

We believe a trial is essential for the following reasons: first an adequately powered RCT employing radiotherapy techniques ensuring adequate coverage of the entire portal tract will establish whether PIT should be offered routinely to patients with MPM after chest wall intervention in the era of palliative chemotherapy; second to establish whether chest wall metastases are symptomatic and thus, whether PIT, if effective, is clinically significant.

The hypothesis for this trial is that prophylactic irradiation of tracts will reduce the incidence of chest wall nodules from 15% to 5%. The primary objective of the PIT study is to determine the efficacy, as assessed by the incidence of chest wall metastasis, of prophylactic irradiation of tracts following invasive chest wall intervention in malignant pleural mesothelioma compared to no prophylactic radiotherapy. Secondary objectives include: the description of the toxicity of PIT; time from randomisation to chest wall tract metastasis in patients undergoing PIT compared with the no prophylactic radiotherapy; the assessment of pain from chest wall metastasis.

## Methods and analysis

### Trial design

This is a two-arm, phase III multicentre (list of centres can be found in online supplementary appendix 1 including a mix of academic centres and community hospitals) randomised superiority trial comparing radiotherapy versus no radiotherapy in patients with a histological diagnosis of MPM following chest wall intervention (see figure 1). A total of 374 patients will be randomised on a 1:1 basis to receive PIT (experimental arm) or no PIT (control arm). Patients can receive chemotherapy postradiotherapy/randomisation at the discretion of the treating physician.

**Figure 1 BMJOPEN2015010589F1:**
[figure not shown]
Trial schema/flow chart. MPM, malignant pleural mesothelioma.

The follow-up period for the study is up to 2 years postrandomisation which includes regular telephone follow-up and a minimum of four outpatient visits in the first year.

### Patient selection

Potential participants will be identified by the principal investigator and his/her team at each centre, via the discussion of cases in a multidisciplinary team meeting (MDT). If a patient is identified as a potential participant in the PIT trial they will be approached at their next clinic visit, as part of discussions with the patient about their options for treatment. Patients who are interested in receiving further information about the trial will be given a copy of the patient information sheet (see online supplementary appendix 2) and consent form (see online supplementary appendix 3), and will have the opportunity to discuss the trial in detail before deciding whether to participate.

### Inclusion criteria

Either sex, age ≥18 years.Diagnosis of mesothelioma by MDTAll histological subtypes. Where the histological diagnosis is unclear, a specialist thoracic pathologist should be consulted.Eastern Cooperative Oncology Group performance status 0–2.Inoperable disease or operable disease in patients unsuitable for surgery as decided by a MDT.Chest wall intervention with video-assisted thoracoscopy (VATS), open surgical biopsy, local anaesthetic thoracoscopy or chest drain.Able to start radiotherapy within 42 days (6 weeks) from most recent chest wall intervention.Chest wall intervention scar visible at time of randomisation.No indwelling pleural catheters in situ at the intervention site.Radiotherapy target volume acceptable by the local radiotherapist.No previous open thoracotomy.No previous radiotherapy to the region of the chest wall intervention site.Not currently receiving chemotherapy and not received chemotherapy for mesothelioma before randomisation.No other previous or concomitant illness or treatment which in the opinion of the clinician will interfere with the trial treatments or comparisons.Patients enrolled on other clinical trials could be considered after discussion with the chief investigators.Female patients must satisfy the investigator that they are not pregnant, or are not of childbearing potential, or are using adequate contraception.Patients must not be breastfeeding.Absence of any psychological, familial, sociological or geographical condition potentially hampering compliance with the trial protocol and follow-up schedule; those conditions should be discussed with the patient before randomisation in the trialPatients can only be randomised in this trial once.

### Exclusion criteria

Patients who underwent a thoracotomy (as large thoracotomy scars may not be adequately covered by this radiotherapy technique).Previous radiotherapy to the region of the chest wall intervention site.Indwelling pleural catheter in situ at the intervention site.Patients currently receiving chemotherapy.

### Consent

All patients will be informed of the aims of the trial, the procedures and possible adverse effects, and the mechanism of treatment allocation. Patients will be informed as to the strict confidentiality of their patient data, but that their medical records may be reviewed for trial purposes by authorised individuals other than their treating physician.

It will be emphasised that the participation is voluntary and that the patient is allowed to decline further participation in the protocol whenever he/she wants. This will not prejudice the patient's subsequent care. Documented informed consent will be obtained by local principal investigators or a delegated member of staff for all patients included in the trial before they are registered or randomised in the trial in accordance with the national and local regulatory requirements.

### Randomisation procedure

Patients will be randomised by phone or fax on a 1:1 basis to one of two treatment arms. A variant of an adaptive biased coin randomisation method will be used to favour balance between treatment arms in the four strata formed from the following two factors:
Histology (epithelioid or not epithelioid)Intention to give chemotherapy

Randomisation will be undertaken centrally by Manchester Academic Health Science Centre Clinical Trials Unit (MAHSC-CTU).

### Radiotherapy

Patients are treated on a linear accelerator using a single electron field. Treatment fields can be shaped using individualised lead cut-outs of the appropriate thickness. The total dose of radiotherapy in the PIT arm is 21 Gy in three fractions, once daily over three consecutive days. The patient can be treated supine, prone or in the lateral position depending on the position of the chest wall intervention site. To ensure >90% of the prescribed dose is delivered to the skin surface, 0.5 cm tissue-equivalent bolus can be applied to the whole treatment field. The field position for radiotherapy is recorded so that if the patient develops chest wall nodules it can be determined if the nodules are inside or outside the treatment field.

The clinical target volume (CTV) comprises the visible and palpable scar with a 1 cm margin of clinically normal tissue in the lateral, medial and inferior directions at the skin surface. The planning target volume (PTV) comprises the CTV with a 1 cm margin in all directions at the skin surface. The CTV to PTV expansion allows for set up errors, changes in the electron beam profile at depth and patient motion. The treatment field is defined by adding a further 1 cm margin in all directions to account for the beam penumbra.

The superior margin will vary and should be the determined by counting three ribs superiorly. The upper border of the third rib superior to the scar will be the superior border of the treatment field. This will take into account microscopic spread but also ensure that chest wall intervention tracts (which will commonly run over the rib superior to the scar) are covered at depth (see figure 2).

**Figure 2 BMJOPEN2015010589F2:**
[figure not shown]
Prophylactic irradiation of tracts radiotherapy field margins.

No organs at risk need to be identified and if a patient has two intervention sites, and therefore two scars (eg, a VATS scar and adjacent chest drain scar) these can be treated within a single treatment field or two separate fields. A gap of >1 cm must separate two treatment fields.

### Chemotherapy

Patients can be treated with palliative chemotherapy at the physician's discretion after completion of radiotherapy (experimental arm) or after randomisation (control arm). The efficacy and/or safety of chemotherapy is not being investigated as part of the study. The chemotherapy regimen used should be cisplatin or carboplatin plus pemetrexed, although alternative chemotherapy regimens (including clinical trial agents) may be considered after discussion with the chief investigators. The number of cycles given is left to the physician's discretion. A gap of at least 1-week must separate the completion of radiotherapy and the start of palliative chemotherapy. The chemotherapy regimen, start and stop dates and total number of cycles administered should be recorded. No further data needs to be collected concerning the patients chemotherapy treatment.

Concomitant medication-not applicable for this trial.

### Discontinuation or withdrawal of patients

In the case of disease progression, the patient will be treated according to each centre's policy. For patients allocated to the treatment arm, radiotherapy can be stopped at the participants request or if too unwell to continue at the discretion of the treating clinician.

### Outpatient visits

The patient is reviewed in clinic 6, 12, 26 and 52 weeks following randomisation to assess for any signs of chest wall metastasis and to record any treatment-related toxicities. In addition, telephone follow-up at 4-weekly intervals following randomisation will determine if the patient has noted any chest wall nodules. If a patient is suspicious that a nodule has appeared, they will be invited to clinic for assessment.

If a chest wall metastases is confirmed, the position of the metastases is recorded in relation to the reconstructed radiotherapy treatment field.

Patients are asked to complete a visual analogue score (VAS) for pain at baseline, and at each telephone and clinic follow-up. Patients are specifically asked to only consider pain at the original site of chest wall intervention. If the patient develops chest wall nodules they will be asked to complete a VAS for pain at the site of the chest wall intervention at for the three nodules closest to the original intervention.

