### Outcome measures

The primary end point is the incidence of chest wall tract metastasis 6 months from randomisation. If a patient raises suspicion that a chest wall nodule had developed at telephone follow-up, they will be invited to attend an outpatient appointment with the investigator. If there is clinical evidence of a chest wall metastases, a chest wall metastasis cardio respiratory fitness (CRF) is completed using the clinic date as date of chest wall metastasis.

The secondary end points are:
Time from randomisation to chest wall tract metastasis (recorded on chest wall metastasis CRF)Position of chest wall tract metastasis recurrence in relation to radiotherapy field in patients randomised to experimental arm (in field/out-of-field, recorded on chest wall metastasis CRF)Acute and late skin radiotherapy toxicity (recorded by CTCAE v4.0 at baseline and at each outpatient visit on CRF)Pain from chest wall tract metastasis (recorded by VAS pain scores recorded on chest wall metastasis CRF)

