#### Toxicity

Skin toxicity will be assessed according to NCI Common Terminology Criteria for Adverse Events V.4.0. The proportions of patients experiencing a grade of 3 or above acute toxicity, including acute radiation morbidity, or late radiation morbidity will be compared between the treatment groups using a two-sided χ^2^ test with a 5% level of significance. Acute toxicity will be defined as toxicities occurring from start of treatment to 3 months after completion; late toxicity will be defined as toxicities occurring between 3 months and 2 years after completion of treatment.

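### The toxicity sections conflict on whether skin events count only when attributed to treatment, and the attribution wording biases the between-arm test towards showing harm from PIT

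*Protocol article*

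**What the plan says.** Four places in the protocol article bear on this point.

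- **Outpatient visits.** Patients attend at 6, 12, 26 and 52 weeks after randomisation "to assess for any signs of chest wall metastasis and to record any treatment-related toxicities".
- **Outcome measures.** The secondary end point is "Acute and late skin radiotherapy toxicity (recorded by CTCAE v4.0 at baseline and at each outpatient visit on CRF"). The name refers to radiotherapy. The schedule includes a baseline grade and is not limited to one arm.
- **Analysis, Toxicity.** "Skin toxicity will be assessed according to NCI Common Terminology Criteria for Adverse Events V.4.0", with no mention of cause. The variable tested is the proportion of patients with a "grade of 3 or above acute toxicity, including acute radiation morbidity, or late radiation morbidity will be compared between the treatment groups", by a two-sided chi-square test at 5%.
- **Trial design.** This is a "randomised superiority trial comparing radiotherapy versus no radiotherapy", so control patients receive no PIT.

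The Introduction states the corresponding objective as describing the toxicity of PIT.

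**The concern.** A randomised control arm lets background skin events (wound problems, effects of the chemotherapy allowed in both arms) be subtracted from those seen after PIT. That works only if both arms are counted by the same rule.

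Consider the same grade 3 skin reaction near the scar at week 6 in two patients. In the PIT arm, a clinician who can know the allocation may call it treatment-related, and it counts. In the control arm there is no trial treatment to relate it to, so under the clinic-visit wording it may never be entered. The late component is plainer still: radiation morbidity requires radiation.

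At stake is a stated secondary objective, the toxicity that will be weighed against any benefit of PIT. The primary end point and the sample size are not affected.

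**Working it through.** **Step 1: the wordings side by side.**

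| Section | Points to attribution | Points to any-cause grading |
|---|---|---|
| Outpatient visits | records toxicities related to treatment | not limited to one arm |
| Outcome measures | named as radiotherapy toxicity | CTCAE grade at baseline, before any radiotherapy, and at each visit |
| Toxicity | late component is radiation morbidity | skin graded by CTCAE with no causal condition; the acute component includes radiation morbidity, so it is wider than it |

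A baseline grade makes sense only if skin is graded whatever the cause. A record of treatment-related toxicity makes sense only if it is not. Sites following different sections would record different events.

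**Step 2: the plan's own figure.** The article gives no figure for the toxicity comparison. Its sample size does reproduce: 15% v 5%, two-sided 5%, 80% power, no continuity correction gives 141 per arm, 282 in all, against 280 stated (power at 140 per arm is 0.7997). Then 280 / 0.75 = 373.3, rounded up to 374. Half of 374 is 187 per arm, which is used below.

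**Step 3: how few attributed events reach significance if no control event is counted.** For k events in 187 against 0 in 187, the uncorrected statistic is 374k / (374 − k).

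| k v 0 | Chi-square | p, uncorrected | p, Yates | p, Fisher |
|---|---|---|---|---|
| 3 | 3.02 | 0.082 | 0.246 | 0.248 |
| 4 | 4.04 | 0.044 | 0.132 | 0.123 |
| 5 | 5.07 | 0.024 | 0.072 | 0.061 |
| 6 | 6.10 | 0.014 | 0.040 | 0.030 |

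Four events suffice uncorrected, and six with Yates or Fisher. The article does not say which form of the test is meant.

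**Step 4: chance of rejecting with no true harm.** Assume the same background grade 3+ rate r in both arms, no radiotherapy effect, a share f of PIT-arm events attributed, and no control events counted. The PIT count is then Binomial(187, r × f). The rejection probability is P(count ≥ 4) uncorrected, or P(count ≥ 6) with Yates or Fisher. For example, r = 2% and f = 1 give an expected 187 × 0.02 = 3.74 events against 0.

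| Assumed r | f = 1, uncorrected | f = 1, Yates or Fisher | f = 0.5, uncorrected | f = 0.5, Yates or Fisher |
|---|---|---|---|---|
| 1% | 12% | 1% | 1.5% | 0.04% |
| 2% | 52% | 17% | 12% | 1% |
| 3% | 81% | 49% | 31% | 6% |

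If events of any cause are counted in both arms, exact enumeration of the uncorrected test gives 3.8%, 4.5% and 4.7%, close to the nominal 5%. The article gives neither r nor f; both are assumptions.

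**The case against.** The tempting stronger reading is that toxicity is recorded only when judged treatment-related, so a control patient scores zero by definition and the test measures attribution alone. The article does not support it:

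- The clinic-visit sentence states the purpose of the visits and does not say only.
- Skin grades are taken at baseline and at every clinic visit, with no limit to one arm.
- The acute variable is wider than radiation morbidity, so a grade 3 event in a control patient can count.
- Treatment-related is not defined as radiotherapy-related, and controls may receive chemotherapy.
- Safety reporting defines an adverse event without requiring causality and writes an explicit radiotherapy-relatedness condition into four of the serious-event criteria. The authors can write such a filter when they want one.

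All of this stands against a structural zero for acute toxicity. It does not remove the conflict. The clinic-visit wording does carry a relatedness condition, and the end point is named for a treatment that one arm does not receive. Reading treatment-related to include chemotherapy leaves an asymmetry: a wound event in a control patient not on chemotherapy has no treatment to be related to, while the same event after PIT does. The Chemotherapy section also says that the safety of chemotherapy is not under study.

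It is also fair to say that the rejection rates stack unfavourable assumptions, that they shrink sharply with Yates, Fisher or partial attribution, and that several then fall below 5%. They show what could happen and are not an estimate.

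Finally, test detail and form instructions may sit in documents not shown. But the point rests on wording that is stated, and no analysis plan can recover control events that clinics did not record.

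**Conclusion.** Wrong as written. The Outpatient visits, Outcome measures and Toxicity sections conflict on whether toxicity is counted by attribution. Where the attribution wording is followed, control events tend to be under-counted, and late radiation morbidity cannot occur in controls at all, so the planned comparison is biased towards excess harm from PIT.

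The direction follows from the text; the size does not. The worst-case figures of 12%, 52% and 81% (uncorrected), or about 1%, 17% and 49% (Yates or Fisher), rest on 187 analysed patients per arm, no control events counted, full attribution in the PIT arm, and assumed background rates of 1%, 2% and 3%. With half attributed, they are 1.5%, 12% and 31% uncorrected. The consequence is confined to a secondary comparison.

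**What to change.** - **Outpatient visits:** record skin events at the intervention site by CTCAE v4.0 in both arms at each clinic visit, whatever the presumed cause.
- **Outcome measures and Toxicity:** base the between-arm test on any-cause grade 3+ skin events that are worse than the patient's own baseline grade.
- **Attributed toxicity:** report investigator-attributed radiotherapy toxicity, including late radiation morbidity, descriptively and in the PIT arm only. This matches the descriptive objective in the Introduction.

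The cost is a change of wording and an instruction for completing the case report form; the visits and the grading scale stay the same. The downside is a few more recorded events, some due to chemotherapy or wound problems, and a slightly noisier comparison.
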